**Sample size calculation**

To demonstrate an improvement of 5% in the active intervention group vs 1% in the control group in exercise tolerance (expressed in percentage exercise tolerance compared to what can be expected given the patient’s age and sex) would require 99 patients in the control group and 198 in the active intervention group (SD10%, alpha=0.05, power=0.90, ratio experimental to controls=2). Even if only 50% of patients in the experimental group adhere to the training, we would in the as-treated analysis compare three groups of each 99 patients, which would give us a power of 0.80. To account for non-adherence and loss to follow-up a total of 330 patients will be randomized. This number of patients will be sufficient to demonstrate a smaller difference (5% vs 2%) in a repeated measurements analysis with a power of 75-90% (2 follow-up measurements, correlation between follow up measurements=0.70, correlation between baseline & follow-up=0.50).

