### Other study parameters (if applicable)

We will document and adjust for baseline levels of traditional cardiovascular risk factors (blood pressure, smoking, lipids levels, body mass index), pre-existing anxiety and depression at baseline, and social economic status.
In the active intervention group we will monitor adherence to the online mindfulness training through the frequency of logging onto the website. In both active intervention and control group we will monitor participation in other mindfulness-based programs, practice of mindfulness-based exercises, and use of complementary care (through a modified Tic-P questionnaire).

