## Withdrawal of individual subjects

Subjects can leave the study at any time for any reason if they wish to do so without any consequences. The investigator can decide to withdraw a subject from the study for urgent medical reasons. If a patient decides to withdraw, the investigator will ask the patient consent for including the data collected thus far in the analysis.

A potential problem would arise if a large group of patients randomized to the active intervention are non-adherent to the active intervention. Nevertheless, non-adherence is considered part of what can be expected in the future when such an intervention is implemented in everyday practice and thus effectiveness rather than efficacy is measured.

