# STATISTICAL ANALYSIS

## Descriptive statistics

Descriptive statistics will be calculated to describe the study population and to determine if any chance differences exist between the groups. Formal tests for differences will not be performed since we trust that the randomization procedure will be properly performed. Missing values will be imputed with a multiple imputation approach. The results will be tabulated.

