## Univariable analysis

Short-term results (3 months) and mid-term results (1 year) will be calculated. Differences in mean improvements between the groups will be calculated for all outcome measures expressed on a continuous scale. Analysis with repeated measurement methods (mixed models) will be performed to account for multiple measurements performed during follow-up and for missing values.

Survival analysis will be performed with a failure being an event as defined according to the composite endpoint.

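### The methods named for missing walk tests make no provision for recorded training adherence, so the effect of offering the training would be overstated if non-adherers are lost more often and adherers benefit

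*Protocol*

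**What the plan says.** The intention-to-treat analysis (Protocol 9.2) asks whether offering the training works and keeps non-adherent patients in the active arm. Section 7.4 gives the reason: "non-adherence is considered part of what can be expected in the future when such an intervention is implemented in everyday practice".

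Two statements cover missing data:

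- Section 9.3, for the continuous outcomes: "Analysis with repeated measurement methods (mixed models) will be performed to account for multiple measurements performed during follow-up and for missing values".
- Section 9.1, under descriptive statistics: "Missing values will be imputed with a multiple imputation approach".

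Neither lists model terms or imputation variables, and nothing says which one governs the primary comparison.

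Adherence is recorded from the online programme. Section 5.1 documents whether the questions were completed, and section 7.1.3 says: "In the active intervention group we will monitor adherence to the online mindfulness training through the frequency of logging onto the website". Section 9.2 uses it in three places: to form the on-treatment and partially treated groups, as a continuous proportion of exercises completed, and in a structural model that corrects for non-compliance. No intention-to-treat analysis mentions it.

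The sample size paragraph in section 4 considers the case "Even if only 50% of patients in the experimental group adhere to the training". Section 7.6, on follow-up of subjects withdrawn from treatment, contains only the entry None.

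**The concern.** A mixed model with arm, visit and walk tests predicts a lost active-arm patient from retained active-arm patients with similar earlier tests. That is sound if, given those tests, the lost and the retained would have fared alike. It fails if patients who abandon the training are also more likely to miss the clinic tests and gain less than adherers. The retained group is then richer in adherers, and the model moves from the effect of offering the training towards the effect under better adherence. The control arm has no counterpart to this mechanism.

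The trial holds the variable that would separate the two kinds of patient. It comes from the website, so it exists even for an active-arm patient who never returns to the clinic. The training runs 12 weeks and the first follow-up test is at 3 months, so a patient may stop training and be lost with only a baseline test on record. Under section 9.6 the 3-month and 1-year results decide whether the long-term economic model is built, and trial data feed that model.

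**Working it through.** **Inputs from the protocol (section 4).** "To demonstrate an improvement of 5% in the active intervention group vs 1% in the control group in exercise tolerance", a difference of 4 points; "SD10%, alpha=0.05, power=0.90, ratio experimental to controls=2"; 330 randomised; correlation 0.70 between follow-up tests and 0.50 between baseline and follow-up.

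**The plan's own figures.** Controls needed, two-sided: (1.960 + 1.282)² × 10² × (1 + 1/2) / 4² = 98.5, so 99, with 198 active. This agrees with "would require 99 patients in the control group and 198 in the active intervention group". The total is 297, and 297 / 0.90 = 330, so the margin equals a 10% allowance. The protocol says it covers non-adherence and loss together. The as-treated power of 0.80 also reproduces: with 99 versus 99 and a difference of 4, power is 0.804. The plan's as-treated calculation therefore gives adherers a 4-point advantage over controls, and that value is used here.

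**Assumptions not in the protocol.** Adherence is a = 0.5, the protocol's stress case. Non-adherers gain 1, as controls do. Loss depends on adherence only, at rate l in adherers and m in non-adherers. The true effect of offering is then 0.5 × 4 = 2.0.

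**Loss before month 3.** Only baseline is available for the lost patients, so the estimate follows the adherer share among the retained:

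estimate = 4 × a(1 − l) / [a(1 − l) + (1 − a)(1 − m)]

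Standard error at 99/198: 10 × √(1/99 + 1/198) = 1.23. It is used throughout as a yardstick.

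| Active-arm loss | Pattern | l, m | Estimate | Excess | Excess in SE |
|---|---|---|---|---|---|
| 10% | non-adherers lost twice as often | 0.067, 0.133 | 4 × 0.4667/0.9 = 2.07 | 0.07 | 0.06 |
| 10% | three times as often | 0.05, 0.15 | 4 × 0.475/0.9 = 2.11 | 0.11 | 0.09 |
| 10% | all losses non-adherers | 0, 0.20 | 4 × 0.5/0.9 = 2.22 | 0.22 | 0.18 |
| 20% | twice as often | 0.133, 0.267 | 4 × 0.4333/0.8 = 2.17 | 0.17 | 0.14 |
| 20% | three times as often | 0.10, 0.30 | 4 × 0.45/0.8 = 2.25 | 0.25 | 0.20 |
| 20% | all losses non-adherers | 0, 0.40 | 4 × 0.5/0.8 = 2.50 | 0.50 | 0.41 |

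**Loss after the 3-month test.** The observed 3-month value carries part of the information. Its regression weight given baseline is (0.70 − 0.50²)/(1 − 0.50²) = 0.60, so about 40% of the gap remains for each lost patient. If all losses are non-adherers, the excess at 1 year is about 0.10 × 2.22 × 0.40 = 0.09 at 10% loss and 0.20 × 2.50 × 0.40 = 0.20 at 20%. The estimates are then about 2.09 and 2.20. Large simulations gave 2.05 to 2.08 and 2.19 to 2.20.

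**With adherence in the imputation model.** In simulations where loss depended on adherence alone, the estimate returned to 2.0 within simulation error (1.97 to 2.01), for early and late loss alike.

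**Other cases.** If adherers gain nothing over controls, the factor 4 becomes 0 and so does the bias. If adherers are lost more often, its sign reverses. If 4 points is instead read as the effect in the whole active arm at 50% adherence, adherers must gain 8 over controls. The worst early-loss cases are then 4 / 0.9 = 4.44 and 4 / 0.8 = 5.00, the same percentage inflation (11% and 25%), or 0.36 and 0.81 SE.

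**The case against.** The strongest objection is that this is analysis-plan content. Section 9.1 lists no imputation variables and section 9.3 no model terms; both are commonly fixed in a statistical analysis plan, which is not shown here. A reader might infer that the plan ignores adherence when it handles missing data. The text does not support that, because adherence could be among the imputation variables. What stands is narrower. Section 9.3 positively assigns missing values to a mixed model, section 9.1 names another method without ranking the two, and the only analyses given the adherence data are those in section 9.2 outside the intention-to-treat comparison.

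The second objection is that the driver is assumed. No section gives loss by adherence. Patients are recruited from those already attending the clinic for periodic follow-up, and the training is online, so dropping it need not mean missing a clinic test. A reader might infer from the section 7.6 entry that patients who stop training are not followed. It is a single unelaborated word and gives no rate. This objection stands: an upward bias is possible, not shown.

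Third, a reader might infer that each lost patient is treated as the average retained one. That is not so. The baseline test is conditioned on, and an observed 3-month test removes more than half of the error.

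Fourth, the recovery of 2.0 is built into the simulation. If loss also depends on unobserved decline in walking, using adherence does not guarantee an unbiased estimate. This also stands.

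**Conclusion.** The point holds in conditional form. Nothing stated for the intention-to-treat analysis uses recorded adherence, and a plain mixed model would overstate the effect of offering the training if two things are both true: non-adherers are lost more often, and adherers benefit. The protocol states neither.

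At the loss the sample size allows for, the excess is small, at most 0.22 points on a true 2.0. It becomes material only if loss is about double that allowance and falls almost wholly on non-adherers before month 3. These sizes rest on 50% adherence, a 4-point gain in adherers and no gain over controls in non-adherers. The evidence supports a low-cost improvement. It does not support a claim that the primary result will be biased.

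**What to change.** State in section 9.3 that, for the intention-to-treat walk-test analysis:

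- missing 3-month and 1-year values are multiply imputed separately by arm, from baseline and available follow-up walk tests;
- in the active arm, the proportion of exercises completed (or log-ins) is added as an auxiliary variable, in the imputation model only and not in the treatment comparison;
- the repeated-measures comparison by randomised arm is run on the imputed data;
- the plain mixed model is kept as a sensitivity analysis.

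This also settles which of the two named methods governs the primary analysis.

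The cost is wording, since the protocol already plans to collect the data. The imputation model becomes somewhat larger, and the estimate may be slightly less favourable or less precise. Bias is removed only to the extent that loss depends on recorded adherence and observed walk tests.

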## Multivariable analysis

Multivariable analysis will be performed to adjust for any chance differences in risk factors at baseline that can clinically be expected to affect the outcome, for congenital heart disease vs cardiomyopathy, and for socio-economic status and to test for interaction effects. Furthermore, we will test for a differential effect on outcome depending on the level of pre-existing anxiety and depression.

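### Beyond diagnosis and socio-economic status, section 9.4 adjusts for factors that differ by chance at baseline, whereas section 7.1.3 commits to a fixed list; one pre-specified list should stand in both

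*Protocol*

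**What the plan says.** Three places in the protocol bear on the adjusted analysis.

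- **Section 7.1.3, Other study parameters:** "We will document and adjust for baseline levels of traditional cardiovascular risk factors". Four are named (blood pressure, smoking, lipids, body mass index), followed by "pre-existing anxiety and depression at baseline, and social economic status". No condition on balance is attached.
- **Section 9.4, Multivariable analysis:** the model will "adjust for any chance differences in risk factors at baseline that can clinically be expected to affect the outcome". It then adjusts "for congenital heart disease vs cardiomyopathy, and for socio-economic status and to test for interaction effects", and those two factors carry no imbalance condition. Anxiety and depression are named in 9.4 only as possible modifiers of the treatment effect.
- **Section 9.1, Descriptive statistics:** one purpose of the baseline description is "to determine if any chance differences exist between the groups". It adds: "Formal tests for differences will not be performed". No numerical criterion for a difference is given anywhere.

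**The concern.** Read together, 9.1 looks for chance differences and 9.4 adjusts for those it finds. If body mass index, say, turns out balanced, 7.1.3 puts it in the model and 9.4 leaves it out. Two different adjusted results could then both be called planned. Because there is neither a test nor a threshold, entry would be by inspection.

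The imbalance rule is also the weaker one on statistical grounds, even for an analyst who never sees the outcome. A prognostic factor that happens to be balanced hardly moves the estimate. If it is omitted for that reason, the variance it explains still stays in the residual and hence in the standard error. The reported standard error then overstates the true variability of the estimate. What is at stake is the calibration and precision of the adjusted treatment effect, using baseline data that the trial collects anyway.

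**Working it through.** **1. The two covariate sets**

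| Factor | 7.1.3 | 9.4 |
|---|---|---|
| Blood pressure, smoking, lipids, body mass index | always | if a chance difference is seen |
| Baseline anxiety, depression | always | not named for adjustment; at most if a chance difference is seen |
| Socio-economic status | always | always |
| Diagnosis (congenital vs cardiomyopathy) | not listed | always |

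The union has eight factors: seven in 7.1.3 (counting anxiety and depression separately) plus diagnosis. Under 9.4, two are always in and six are conditional.

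**2. The plan's own figure.** The sample size section sets out "To demonstrate an improvement of 5% in the active intervention group vs 1% in the control group in exercise tolerance", so the difference is 4 points, with SD 10, alpha 0.05, power 0.90 and ratio 2:1. Two-sided, the control group needs

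n = (1.960 + 1.282)² × 10² × (1 + 1/2) / 4² = 98.5, rounded up to 99, with 198 active.

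This reproduces the stated 99 and 198. Power at these sizes is 0.901. No covariate adjustment enters the calculation.

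**3. An upper bound on the widening, by arithmetic.** Let the eight covariates be independent, of equal weight, and jointly explain a share R² of the outcome variance. R² is an assumption; the protocol gives none.

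- All eight in the model: residual variance is proportional to 1 − R².
- Only the two fixed ones in the model: 1 − R²/4.
- Ratio of interval widths, ignoring degrees of freedom: √[(1 − R²/4)/(1 − R²)].

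Results:

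- R² = 0.30: √(0.925/0.70) = 1.15
- R² = 0.10: √(0.975/0.90) = 1.04
- R² = 0.05: √(0.9875/0.95) = 1.02

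These are ceilings, because in practice some of the six conditional factors will be imbalanced and enter.

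**4. Simulation of the rule.** Settings: 198 vs 99, SD 10, eight covariates, two always included, the other six entered when the absolute standardised difference exceeds 0.1 or 0.2. The thresholds are assumptions too. The comparison is with always entering all eight.

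| R² | Interval width vs fixed list | Level (nominal 0.05) | Power for 4 points |
|---|---|---|---|
| 0.30 | 9-13% wider | about 0.037-0.040 | about 0.93-0.95, against 0.97 |
| 0.10 | 2-3% wider | near nominal | about 1 point lower |
| 0.05 or less | about 1% wider or less | nominal | no meaningful loss |

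As an example, at R² = 0.30 and threshold 0.2 the mean width is 4.63 against 4.11, and 4.63/4.11 = 1.13. All rows lie below the ceilings in step 3.

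Treating all eight as conditional would give 4.80 against 4.11, or 17% wider. That is not the rule in 9.4, which fixes two of them.

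**5. Direction under other settings.** With 220 vs 110 patients, six covariates all subject to selection, R² = 0.30 and threshold 0.1:

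- Type I error is 0.032 with selection and 0.047 with the full list.
- Coverage is 0.968 and 0.953.
- Power for 4 points is 0.930 unadjusted, 0.965 with selection and 0.982 with the full list.

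Selection therefore still beats no adjustment here. It falls short only of the fixed list.

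**The case against.** **The two sections may be compatible.** The sentence in 9.4 can be read as giving the purpose of adjustment (to remove the influence of chance differences), with 7.1.3 naming the factors. That reading is possible. But 9.1 sets out to find whether such differences exist, which favours selection. The purpose reading also leaves diagnosis missing from 7.1.3 and leaves 9.4 without named risk factors. The same one-sentence edit settles either reading.

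**The covariate set belongs in the SAP.** Silence here would be no fault. The protocol is not silent, though: it states two rules, and a SAP that followed one would depart from the other.

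**The effect may be nil.** This stands in part. The outcome is change in a walk distance already scaled to age and sex, and factors that predict the level need not predict the change. If they explain 5% or less, nothing of note is lost.

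**Stronger readings that the protocol does not support.** A reader might infer any of the following:

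- That 9.4 adjusts solely for imbalanced factors. It does not: diagnosis and socio-economic status always enter.
- That selection on imbalance creates false positives. It does not: made without sight of the outcome, it errs towards conservatism.
- That the trial loses power against its plan. It does not: the loss is relative to the fixed list, and at R² of 0.10 or 0.30 power under the selection rule stays above 0.90.
- That the primary comparison is compromised. Section 9.3 estimates differences in mean improvement without these covariates, and nothing names the 9.4 model as primary.

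**Conclusion.** The point holds as an inconsistency between 7.1.3 and 9.4, and as a weaker choice of rule in 9.4 for the six factors other than diagnosis and socio-economic status. Its effect is confined to the adjusted analysis and runs in the conservative direction.

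The size ranges from negligible to clear, depending on a prognostic strength that the protocol does not state. The figures further assume independent covariates of equal weight, entry thresholds of 0.1 or 0.2, and selection made blind to the outcome. With no written threshold, that last assumption is not secured by the text, so the choice of covariates is also open to judgement.

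This should be corrected because the remedy is nearly free. It is not a threat to the trial's main conclusion.

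**What to change.** In 9.4, replace "adjust for any chance differences in risk factors at baseline that can clinically be expected to affect the outcome" with one fixed list. Suggested wording: *The adjusted analysis includes, whatever the observed balance, diagnosis (congenital heart disease or cardiomyopathy), socio-economic status, and the baseline factors listed in section 7.1.3.*

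Add diagnosis to the list in 7.1.3 so that the two sections match. State in 9.1 that the baseline comparison is descriptive only and does not determine which covariates enter the model.

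The cost is one sentence in 9.4 and small alignments in 7.1.3 and 9.1. No new data are needed beyond the baseline factors the protocol already plans to record. The model spends about eight degrees of freedom, which is negligible at about 297 patients.

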## Interim analysis (if applicable)

No interim analysis will be performed.

## Economic Evaluation

If the 3 months and 1-year results indicate effectiveness of the mindfulness training, we will develop a Markov decision model to calculate long-term effectiveness, costs, and cost-effectiveness of offering mindfulness training to patients with structural heart disease. The comparison strategy will be usual care. We will perform the cost-effectiveness analysis from the health care and societal perspective considering a lifetime timeframe.

The model will consider different classes of heart failure, cardiovascular risk factors, cardiac events, quality of life, and costs. Event rates, risk factor changes, quality-of-life, health resource utilization, and cost data obtained from the clinical study will be integrated in the models. All co-investigators will be asked to review the model assumptions and inputs prior to performing the analysis in order to avoid bias. The economic evaluation will be performed in accordance with the Dutch recommendations for cost effectiveness analyses and we will explore UK and USA recommendations and costs in a sensitivity analysis.

Quality of life will be based on results from the trial where possible and where necessary from systematic reviews and Quality of Life catalogues available on the web. Costs that will be considered include direct medical costs (health-care costs for mind-body program, events, admissions, rehabilitation after an event, nursing home care for long-term disability), patient costs (out-of-pocket expenses for the mind-body program, time and travel costs associated with the program), and productivity losses (friction costs). Health-care costs will be estimated by multiplying health-care resource utilization with the cost per unit of resource. Future costs and life years will be discounted.

With the decision model we will calculate the effectiveness, the costs, the incremental cost-effectiveness ratios, the net health benefit, and the net monetary benefit for a number of willingness-to-pay thresholds. We will perform extensive (probabilistic) sensitivity analysis, threshold analysis, and value of information analysis.

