# OBJECTIVES

Primary Objective of this study is to determine whether mindfulness training has beneficial clinical and psychological effects in adult patients with structural heart disease (congenital heart disease or cardiomyopathy).

Secondary Objective is to determine whether offering mindfulness training is effective and cost-effective in adult patients with structural heart disease.

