# METHODS

## Study parameters/endpoints

### Main study parameter/endpoint

It is most likely that the mindfulness training will result in an improved quality of life. In this study we set out to search for an even more ambitious goal, and that is to find effects on physical variables. The 6 minute walk test has been chosen as primary outcome since it is a measure of cardiac and overall physical fitness. We expect that the mindfulness training will improve cardiac and overall physical fitness through the mindful breathing exercises, by encouraging a healthy lifestyle, and by reducing chronic anxiety and stress levels.

Primary outcome will be differences between the active intervention and control groups in the mean improvement at 3 months and 1 year, compared to baseline, of age- and sex expected exercise tolerance.

Exercise tolerance will be measured at baseline, 3 months and 1 year with the 6-minute-walk test (in which the distance is measured that a patient can walk within 6 minutes).

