## Intention-to-treat and as-treated analysis

An intention-to-treat analysis will be performed to address whether offering mindfulness training is effective and cost-effective. Patients that are non-adherent to the offered training (cross-overs to usual care) will be analyzed as part of the active intervention group. Similarly, control patients who seek interventions on their own will be analyzed in the usual care group to which they were allocated.

An as-treated analysis will be performed to address whether mindfulness training is beneficial if actually performed and the treatment effect depending on the degree of adherence. The usual care group will consist of the control group. In the active intervention group, adherence to the intervention is monitored (see ‘’Intervention’’) and completion of sufficient number of training modules will be the criterion to determine which patients in the active intervention arm are included in the ‘’on-treatment’’ group. The ‘’on-treatment’’ group will consist of those patients who complete 50% or more of the exercises in the first 12 weeks. Patients who start the mindfulness training but complete less than 50% of the assignments in the first 12 weeks will be considered non-adherent and analyzed separately as the “partially treated’’ group. We will also evaluate outcome as function of the proportion of completed exercises as a continuous variable adjusting for potential confouders in a multivariable model. Finally, we will use the method developed by Robins and Tsiatis that corrects for non-compliance in randomized trials using rank preserving structural failure time models [25-26].

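### Cost-effectiveness is an unconditional secondary objective, but the only economic evaluation with a described method is run only if the results look effective, by a criterion that is not defined

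*Protocol*

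**What the plan says.** The objective carries no condition. Protocol section 2: "Secondary Objective is to determine whether offering mindfulness training is effective and cost-effective in adult patients with structural heart disease". The objective in the Summary is likewise unconditional.

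Section 9.2 repeats the commitment: "An intention-to-treat analysis will be performed to address whether offering mindfulness training is effective and cost-effective". It gives no method for the cost-effectiveness part.

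The method is in section 9.6, which begins: "If the 3 months and 1-year results indicate effectiveness of the mindfulness training, we will develop a Markov decision model". The trial inputs to that model are listed: "Event rates, risk factor changes, quality-of-life, health resource utilization, and cost data obtained from the clinical study will be integrated in the models". The summary measures of cost-effectiveness come from the same model: "With the decision model we will calculate the effectiveness, the costs, the incremental cost-effectiveness ratios, the net health benefit, and the net monetary benefit". Probabilistic sensitivity analysis and value-of-information analysis belong to the same plan.

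Section 7.1.2 lists preference values (EQ-5D-5L, SF-6D, a rating scale), health-care costs and related non-health-care costs (Tic-P) as secondary outcomes, measured at baseline, 3 months and 1 year. Section 9.3 applies to them whatever the result: "Differences in mean improvements between the groups will be calculated for all outcome measures expressed on a continuous scale".

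**The concern.** An unconditional question is answered by a conditional analysis. Whether an intervention is cost-effective depends on the difference in costs and the difference in health utility taken together, with their joint uncertainty. A clinical result that misses significance leaves that open. Section 5.1 argues that the low price (30 euro) gives the programme the potential to be cost-effective, and with a price that low a small utility gain could matter. Value-of-information analysis is most informative when results are uncertain, yet an uncertain result may be what prevents it.

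Because the condition names no outcome, time point rule or threshold, whether to run the evaluation would be decided after the results are known. If the model is built only after favourable results, its trial inputs are selected to some degree for being favourable. Probabilistic sensitivity analysis centred on selected estimates does not remove that.

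At stake is a stated secondary objective, for which utility and cost data are collected from every patient at three visits. The primary analysis and the sample size are not affected.

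**Working it through.** **1. The sections side by side**

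- Section 2 and the Summary: cost-effectiveness is to be determined; no condition.
- Section 9.2: the intention-to-treat analysis addresses it; no condition, no method.
- Section 9.3: separate between-group differences for each continuous outcome; no condition, but costs and effects are not joined.
- Section 9.6: costs and effects are joined in a decision model that is built only if the condition is met.

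So following section 9.6 as written can leave the section 2 objective without a cost-effectiveness result.

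**2. The protocol's own sample size**

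Inputs from the sample size calculation in section 4: "To demonstrate an improvement of 5% in the active intervention group vs 1% in the control group in exercise tolerance", a difference of 4 points; SD 10; alpha 0.05 (taken as two-sided); power 0.90; ratio 2:1.

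n(control) = (1 + 1/2) × (1.960 + 1.282)² × 10² / 4² = 1.5 × 10.51 × 6.25 ≈ 98.5, rounded up to 99, with 198 in the intervention group. This reproduces the stated numbers.

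**3. Illustration of how often the condition could fail**

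Assumption, not in the protocol: the condition means a favourable two-sided p<0.05 on the walk-test difference at one visit.

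SE = 10 × √(1/99 + 1/198) = 1.231. P(condition met) = P(Z > 1.96 − d/SE).

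| True difference d | d/SE | P(met) | P(no model) |
|---|---|---|---|
| 4 | 3.25 | 0.901 | 9.9% |
| 3 | 2.44 | 0.683 | 31.7% |
| 2 | 1.62 | 0.369 | 63.1% |

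The 4 and 3 point differences are the protocol's. The 2 point case is a 4 point effect in adherers, 50% adherence and no effect in non-adherers (4 × 0.5 = 2).

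The answer moves with the reading of the condition:

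- All 330 analysed (110 versus 220, SE 1.168): 7.1%, 27.1% and 59.8%.
- Significance needed at both visits, 99 versus 198, correlation of the two estimates assumed 0.70: P(met) 0.85, 0.57 and 0.25, so no model in 15%, 43% and 75%.
- Repeated-measurements analysis at 3 points, using the protocol's stated power of 75-90%: no model in 10-25%.

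**4. Selection of the model inputs**

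If an input is correlated ρ with the estimate that decides the condition, its average bias, in units of its own SE, is ρ times that estimate's bias in SE units. Under the assumption in step 3, the walk-test estimate given significance is too high by 0.19 SE at d = 4 and by 1.02 SE at d = 2. With ρ between 0.1 and 0.5 (assumed; the protocol gives no value), an input is biased by 0.02 to 0.10 SE at d = 4 and by 0.10 to 0.51 SE at d = 2. The direction is clear if the correlation is favourable; the size is not known.

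**The case against.** The strongest reply is that the condition attaches to a lifetime extrapolation model, and that waiting until there is an effect to extrapolate is a reasonable staged choice. The details of a within-trial cost-utility analysis could properly sit in an analysis plan that is not shown. This stands in part: the lifetime model may remain conditional. It does not remove the conflict, because the protocol places the cost-effectiveness ratios and net benefit inside the conditional model. The objection is to that stated rule, not to missing detail.

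Three stronger readings are tempting, and the protocol does not support them.

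- A reader might infer that the model would be fed an effect inflated by 1.06, 1.21 or 1.63 times at true differences of 4, 3 and 2 points. Those factors describe the walk-test difference given significance at one visit. The walk test is not among the model inputs listed in section 9.6, so they are not the bias in the model.
- A reader might infer that the protocol expects a null walk test with a quality-of-life gain. Section 7.1.1 does say "It is most likely that the mindfulness training will result in an improved quality of life" and calls the physical goal more ambitious, but it goes on to expect better physical fitness too. That outcome is foreseeable, not predicted. Nor would it necessarily block the model: section 2 speaks of clinical and psychological effects, so a quality-of-life gain might itself meet the undefined condition.
- A reader might infer that the utility and cost data would go unused after a null result. Section 9.3 still yields separate differences for them.

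**Conclusion.** The point holds as a conflict between an unconditional secondary objective (sections 2 and 9.2) and a conditional method (section 9.6) whose criterion is undefined. It rests on the text and needs no calculation.

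How often the objective would go unanswered cannot be fixed, because the condition is not defined. The 10%, 32% and 63% are illustrative and hold only for a two-sided 5% test on the walk test at one visit with 99 versus 198 patients; other readings give lower or higher figures. The selection of favourable inputs is a tendency of unknown size and should be reported without an inflation factor. The matter is worth correcting but is confined to a secondary objective.

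**What to change.** State in section 9.6 that a 1-year trial-based, intention-to-treat cost-utility comparison will be done and reported whatever the clinical result: QALYs from EQ-5D-5L and SF-6D, costs from Tic-P and resource use, by randomized arm, with uncertainty. Refer to it from section 9.2, so that the commitment there has an analysis behind it.

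The lifetime Markov extrapolation may stay conditional, provided that the criterion (outcome, time point, threshold) is defined in advance and the report says that the model was run conditionally.

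The cost is a change of wording, plus some analysis time if the clinical result is null. No extra patients, visits or data are needed.
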